## Abstract

**Introduction:**

Breast cancer risk can be substantially reduced with risk-reducing medications (RRMeds). Despite their efficacy, and guidelines which support their use for women at substantially increased risk of breast cancer, they are underused. Barriers to their use in Australia include a lack of awareness of RRMeds by women and clinicians, and a primary care workforce that reports a lack of knowledge and confidence in discussing and/or prescribing these medications. In contrast, Australian clinicians have reported specialist support and guidance as a key facilitator. The Preventing Cancer with Medications (PCMed) Telehealth Service was therefore developed to provide this specialist support and to bridge the evidence–implementation gap. The PCMed Service endeavours to increase the appropriate use of RRMeds and support women and their doctors throughout treatment. The aim of this research is to evaluate the effectiveness, adoption, acceptability, feasibility, fidelity and cost of this new Service, and to determine any adaptations that might be required.

**Methods and analysis:**

The research uses a mixed methods approach. Effectiveness of the PCMed Service will be evaluated by determining whether the PCMed Service is associated with increased uptake of RRMeds compared with historical data. Secondary outcomes include: adoption of the Service, specifically, the proportion of women who attend a PCMed Service consultation; acceptability of the Service for clients and referring clinicians (using a brief survey and semistructured interviews); feasibility and fidelity by evaluating the adherence to the planned Service processes; and the cost, by reporting the difference between funding received per woman and the cost for service delivery.

**Ethics and dissemination:**

This study was approved by the institutional Human Research Ethics Committee (EC00235): HREC/101142/PMCC. The findings will inform future iterations of the Service prior to scaling up. Research findings will be disseminated at scientific meetings and in peer-reviewed journals.

**Trial registration number:**

ISRCTN15718519.

STRENGTHS AND LIMITATIONS OF THIS STUDYA key strength is the theory-informed implementation data collected from participants (clients and clinicians) and the inclusion of cost analyses to aid the future development of the Preventing Cancer with Medications (PCMed) Service.The inclusion of a historical cohort from the same clinics as the prospective cohort (for the primary aim), rather than relying on published data for the preimplementation comparator rates of RRMed uptake is also an important strength.Implementation of the PCMed Service and evaluation are taking place in one large Australian Cancer Centre, thus potentially limiting the generalisability of the findings.

## Introduction

 Globally, breast cancer is the most common cancer in women. In 2020, 2.3 million women were diagnosed with breast cancer and 685 000 women died of the disease.^1^ If the current global trends continue, it is expected that there will be 3 million new cases of breast cancer occurring each year by 2040.^2^ Importantly, this upward trend is not inevitable, as many of these breast cancers are preventable.^3^

Optimal implementation of proven, intensified prevention strategies for women at substantially increased risk of breast cancer, combined with minimising women’s exposure to modifiable risk factors (eg, obesity, alcohol and sedentary lifestyle), will be crucial to lower breast cancer incidence.^3 4^ Approximately 50% of breast cancers occur in the 20% of women who are at increased risk.^5^

Several medications reduce the risk of oestrogen receptor-positive breast cancer.^6^,^17^ These medications include the selective oestrogen receptor modulators (SERMs), tamoxifen and raloxifene, and the aromatase inhibitors (AIs), anastrozole and exemestane (all hereafter referred to as risk-reducing medications (RRMeds)). Guidelines recommend their consideration in individuals who are at moderate to high risk of developing a future breast cancer,^18^,^23^ excluding those with contraindications such as pregnancy, planning pregnancy in the next 3 years, breastfeeding, prior bilateral mastectomy or use of hormone therapy. Additional contraindications include prior thromboembolic events, endometrial cancer (for tamoxifen), smoking, taking anticoagulants or a strong inhibitor of the CYP2D6 enzyme (for SERMs) and premenopausal status or osteoporosis (for AIs).^24^ A single tablet, taken daily for 3–5 years, can reduce the relative risk of breast cancer by between 30% and 60%,^6^,^17^ and the risk reduction persists long after the prescribed treatment period.^8 13 14 16^ Despite strong evidence of efficacy and endorsement in national guidelines,^21^,^23^ the use of RRMeds in Australia is low.^25^ A major barrier to the use of RRMeds is the concern for side effects.^26 27^ Common adverse effects include gynaecological and vasomotor symptoms, menstrual changes, and less commonly, more serious events such as thromboembolism (with SERMs) or endometrial cancer in postmenopausal women (with tamoxifen),^6^ or bone loss (with AIs).^10^ Confusion between RRMeds and chemotherapy,^26 27^ and insufficient information for women to make an informed decision regarding their use,^26^,^30^ suggest that expert medical advice is important for women to weigh the potential benefits and harms in the context of individual risk. Many Australian women at increased risk of breast cancer, and approximately one-third of their primary care physicians (PCPs), are unaware of RRMeds.^27^ Another driver of this evidence–implementation gap in Australia is the lack of a medical workforce capable of, and willing to discuss and prescribe RRMeds.^27^ In one study, among PCPs who were aware of RRMeds, only 3% were very confident in discussing them, and 31% considered it their role to initiate prescribing, although 98% of PCPs would write ongoing prescriptions.^27^ Specialist support has been identified as a key facilitator for PCPs to discuss and prescribe RRMeds.^27^ In response to this, the Preventing Cancer with Medications (PCMed) Telehealth Service has been developed to provide specialist support to PCPs. The ‘knowledge to action’ framework^31^ (figure 1) was adapted to guide the development and implementation of the PCMed Service and its concurrent evaluation.

**Figure 1 F1:**
[figure not shown]
Knowledge creation, as it pertains to the benefits and risks of RRMeds, supports the use of RRMeds as a standard of care. Barriers and facilitators to the uptake of RRMeds have been identified. This research focuses on the steps highlighted in red. AIs, aromatase inhibitors; RRMeds, risk-reducing medications; SERMs, selective oestrogen receptor modulators.

We hypothesise that the implementation of the PCMed Service will be associated with greater use of RRMeds compared with historical controls, and the PCMed Service will be feasible, well-adopted, delivered with fidelity and acceptable to both clients who attend the PCMed Service and to clinicians.

### Intervention—novel PCMed Service

The PCMed Telehealth Service at the Peter MacCallum Cancer Centre (PMCC) in Melbourne is the first of its kind in Australia. It is co-led by a medical oncologist ([name]) and a nurse practitioner ([name]). It is the only specialist service in Australia solely dedicated to delivering comprehensive, personalised information to women to facilitate their informed decision-making about using RRMeds. For women who are suitable and choose to take RRMeds, an initial prescription is provided. The woman, her referring clinician and PCP are offered access to ongoing support to promote sustained use of RRMeds. The PCMed Service intervention is detailed in figure 2.

**Figure 2 F2:**
[figure not shown]
(A) Preservice work-up: referrals are reviewed by the nurse practitioner ([name]). Women who meet preliminary eligibility criteria are sent a questionnaire (regarding demographics, social and medical history, breast cancer risk factors and willingness to consider RRMeds). Breast cancer risk is determined using validated risk prediction models/tools such as iPrevent,^32^ Tyrer Cuzick,^33 34^ or the Breast and Ovarian Analysis of Disease Incidence and Carrier Estimation Algorithm (BOADICEA)^35 36^,unless there is a history of thoracic radiotherapy, in which case risk is estimated using published data.^37^ For women referred from services external to catchment clinics, the iPrevent^32^ prediction model is applied. Eligible women are offered an appointment in the Service. (B) PCMed Service attendance: in the initial telehealth appointment, clients receive a discussion of their personalised breast cancer risk. If a client desires, their 10-year, 20-year or remaining lifetime risk is conveyed as a numerical value. The names and mechanism of action of potentially appropriate RRMeds, the absolute risk reduction that could be achieved with RRMeds, and other benefits and any potential adverse effects of RRMeds are discussed. Client understanding of the information received is assessed. A second consultation is offered for clients requiring more time to decide on whether to take RRMeds. Clients who desire RRMeds receive a prescription and are booked for review in 8–10 weeks to assess and manage any side effects. If tolerating the RRMed, care is transferred to the PCP with additional information and instructions to continue management. (C) Postservice support: a hotline telephone service is provided for clinicians and clients to address any concerns relating to side effects, and additional appointments are made if required. PCMed, Preventing Cancer with Medications; PCP, primary care physician; RRMeds, risk-reducing medications.

Delivered by telehealth, the PCMed Service is intended for women at substantially increased risk of a first breast cancer who are interested in considering taking medications to reduce their risk. Referrals are accepted from clinicians from the PMCC and surrounding services who routinely see women at increased risk of breast cancer. These referring clinics will henceforth be referred to as ‘catchment clinics’; they include Late Effects, Breast Surgical and Familial Cancer Clinics at PMCC and the Familial Cancer Clinic at the Royal Melbourne Hospital. Referrals are also accepted from clinics external to the catchment clinics and from PCPs. Women who attend the PCMed Service are referred to as clients.

### Aims

The overarching aim is to evaluate the effectiveness and process of implementing this new clinical service.

The primary aim is:

To determine whether the PCMed Service is associated with an increased use of RRMeds by women who attend catchment clinics, compared with use by similar women who attended catchment clinics before the implementation of the PCMed Service.

Secondary aims include:

To describe the adoption of the PCMed Service by women who attend catchment clinics. Specifically, the proportion of eligible women who attend the PCMed Service following a catchment clinic appointment where the PCMed Service is discussed.To determine the uptake of RRMeds for all clients who attend the PCMed Service and the associated characteristics.To explore the reasons for not taking up RRMeds and the associated characteristics.To explore the acceptability of the PCMed Service to clients.To explore the acceptability of the PCMed Service to clinicians.To determine the feasibility and fidelity of the PCMed Service intervention and any adaptations required.To evaluate the cost of delivering the PCMed Service from the perspective of the healthcare provider.

## Methods and analysis

### Study design

The process evaluation described here is evaluating this new complex intervention (the PCMed Service) using a mixed methods (qualitative and quantitative) approach. The study has prospective and retrospective components.

### Recruitment to the PCMed Service and study

Prior to the commencement of the PCMed Service, clinicians working in the catchment clinics, including breast care nurses, were informed of the PCMed Service and its concurrent evaluation. Resources were developed and placed in the catchment clinics. These include a client brochure and a clinician fact sheet that describes the Service, eligibility criteria and the referral process.

Eligible women are actively recruited for the PCMed Service from catchment clinics by the nurse practitioner ([name]), who reviews the electronic medical records of women in advance of their catchment clinic appointment and identifies those who are potentially eligible for the PCMed Service. Clinicians seeing these women are reminded by [name] of the PCMed Service and asked to provide eligible women with a client brochure and to refer them to the PCMed Service if appropriate.

#### Inclusion criteria for the study population

Women are eligible if they have no personal history of invasive breast cancer or ductal carcinoma in situ, are aged between 20 and 70 years, and are at substantially increased risk for future breast cancer. Substantially increased risk, for the purpose of this study, is defined as a remaining lifetime risk of at least 20%, or risk in the next 10 years of at least 5%^18^ using any of the three validated risk prediction models commonly used in Australia (ie, iPrevent,^32^ Tyrer Cuzick^33 34^ or the Breast and Ovarian Analysis of Disease Incidence and Carrier Estimation Algorithm (BOADICEA),^35 36^) or a personal history of lobular carcinoma or atypical hyperplasia, or previous thoracic irradiation before age 35 years (and given at least 5 years prior).^37^

Clinicians who see eligible women in the catchment clinics and/or refer to the PCMed Service during the study period will also be recruited to the study to assess the acceptability of the PCMed Service intervention.

#### Exclusion criteria for the study population

Women who have ever taken RRMeds for breast cancer prevention, or who have had a bilateral mastectomy, are ineligible. The PMCC has an established, highly specialised, multidisciplinary Risk Management Clinic^38^ for women who carry (or who are at 50% risk of carrying) a pathogenic variant in a high-risk breast cancer predisposition gene (such as *BRCA1*, *BRCA2*, *PALB2* or *TP53*). Women who are eligible for the PMCC Risk Management Clinic are thus not eligible to attend the PCMed Service (or for this study). Some women with pathogenic variants in moderate-risk genes such as *CHEK2* and *ATM* are eligible for referral to the PCMed Service if they are deemed not eligible for the PMCC Risk Management Clinic.

Clinicians from catchment clinics will be excluded from the study if they are no longer working in the clinic at the end of the study period.

### Outcome measures and data collection

#### Effectiveness of the PCMed Service intervention (primary aim)

The use of RRMeds by similar women before and after the implementation of the PCMed Service will be assessed 12 months after attendance at a catchment clinic. To determine the use of RRMeds prior to the implementation of the PCMed Service, a retrospective chart review is collecting data on consecutive eligible women (historical controls) who attended catchment clinics prior to the commencement of the PCMed Service. For women who attended familial cancer centre catchment clinics, the BOADICEA risk prediction model^35 36^ is routinely applied, and each individual’s risk is documented in their medical record. Other catchment clinics did not consistently apply risk prediction models. Therefore, the first author ([name]) applies one of the three prediction models at the time of data collection (with the choice of prediction model dependent on which is most appropriate based on the available data). First author ([name]) extracts the following data from the medical record for each woman: date of birth, indigenous status, country of birth, socioeconomic status, marital status, parity, education level, whether an interpreter was required, catchment clinic attended, type of clinician seen in the catchment clinic (eg, geneticist, medical oncologist), date of last catchment clinic consultation, whether RRMeds were discussed at that consultation and whether the client had commenced RRMeds within 12 months after the last consultation in the catchment clinic. Comparable data are being collected for the prospective group of women who attend the catchment clinics after commencement of the PCMed Service, regardless of whether they attend the new PCMed Service. For historical controls and those in the prospective cohort, if the first author, [name], is unable to find evidence of a discussion about RRMeds in the woman’s electronic medical record (clinic notes and correspondence), it is presumed that RRMeds were not commenced. It is noted that not all clinicians might routinely document everything discussed in a consultation. Therefore, the prescription history in the medical record is also reviewed. If a discussion about RRMeds is documented, or the prescription history indicates that a RRMed was prescribed, women are contacted to ascertain if RRMeds were commenced within 12 months of that consultation.

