### Statistical considerations and analyses

#### Sample size considerations

The prospective sample size required for the primary outcome will depend on the uptake of RRMeds in the historical cohort. We will identify 100 consecutive historical controls. Based on Australian data,^25^ we expect the uptake of RRMeds in the historical cohort to be 2%. Based on the clinical judgement of the investigators, we consider an increase from a baseline of 2%, prior to the commencement of the PCMed Service, to 20% after its implementation to be clinically significant enough to warrant implementation of this complex intervention. A prospective sample size of 57 clients who attend the PCMed Service from catchment clinics will be required to provide 80% power to detect a minimum change from 2% to 20% at a 5% significance level. To account for a possible 10% loss to follow-up, we will recruit a sample of 63 consenting clients from catchment clinics as they attend the PCMed Service. If the uptake of RRMeds (in the historical cohort) is substantially different from 2%, the prospective sample size will be adjusted.

Recruitment to the Service and the study commenced on 14 November 2023. To date, 100 women (historical controls) have been recruited to the retrospective component of the study and 278 women to the prospective component of the study. Thirty-five of the prospectively recruited women are eligible for the analysis of the primary outcome; the remainder are eligible for other outcome analyses.

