#### Analysis of the primary outcome

##### Effectiveness of the PCMed Service intervention

The proportion of women who start RRMeds within 12 months of a catchment clinic consultation will be summarised preimplementation and postimplementation of the PCMed Service using descriptive statistics. Event proportions will be compared using a χ^2^, Fisher’s exact test or linear mixed modelling as indicated. Differences in the distribution of confounders between the historical and prospective cohorts will be managed using univariable and multivariable logistic, Poisson and/or negative binomial regression and/or linear mixed modelling as indicated.

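### The index visit and the date of the never-user check are not fixed for historical controls, and nothing closes their 12-month window before the Service opened

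*Protocol article*

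**What the plan says.** All references are to the protocol article.

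- **Outcome measures, primary aim.** The general statement is that use of risk-reducing medication (RRMeds) "will be assessed 12 months after attendance at a catchment clinic". For controls, the chart review extracts the "date of last catchment clinic consultation" and "whether the client had commenced RRMeds within 12 months after the last consultation in the catchment clinic". It does not say whether *last* means last before launch or last on record. The prospective group is to have comparable data, with no index visit spelled out.
- **Analysis of the primary outcome.** The summary measure, for both periods, is "The proportion of women who start RRMeds within 12 months of a catchment clinic consultation".
- **Exclusion criteria.** "Women who have ever taken RRMeds for breast cancer prevention, or who have had a bilateral mastectomy, are ineligible". No date is given at which prior use is judged.
- **Who the controls are.** They are "consecutive eligible women (historical controls) who attended catchment clinics prior to the commencement of the PCMed Service". No minimum gap before launch is stated.
- **Launch date.** "Recruitment to the Service and the study commenced on 14 November 2023" (Sample size considerations).
- **Recruitment.** The nurse practitioner screens records ahead of a catchment appointment to find potentially eligible women.

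**The concern.** A proportion starting treatment within 12 months needs a start of the clock, a check at that moment that the woman has not already started, and a follow-up period that belongs to the condition being measured. For the controls, the article names the last visit as the start of the clock, does not date the check, and does not keep follow-up within the period before the Service.

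Two errors can follow, in opposite directions. Counting from the last visit can drop women who started after an earlier visit in the sampling period and came back, which lowers the historical rate and flatters the Service. A window that runs past launch can include starts that the Service itself produced, which raises the historical rate and works against the Service. Regression on measured characteristics cannot restore women whom the index rule has removed.

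The comparator is small, and it also drives the design: the article says the prospective sample size will be adjusted if historical uptake is substantially different from 2%.

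**Working it through.** **1. The plan's own figure.** Inputs from Sample size considerations: 2% against 20%, 5% level (two-sided assumed), 80% power. With equal groups and mean proportion 0.11:

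n = [1.960·√(2·0.11·0.89) + 0.8416·√(0.02·0.98 + 0.20·0.80)]² / 0.18² = (0.867 + 0.357)² / 0.0324 ≈ 46.2.

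The continuity correction gives (46.2/4)·[1 + √(1 + 4/(46.2·0.18))]² ≈ 56.8, so 57 per group. The stated 57 reproduces and is not in dispute.

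**2. What happens to a control who started after an earlier visit and then returned.** Take each possible date for the never-user check:

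| Prior use judged at | Result for this woman |
|---|---|
| Chart review | Excluded, as is every other historical starter. The rate would be zero by construction, so this cannot be meant |
| Last visit | Excluded as an ever-user |
| An earlier visit | Eligible, but her start precedes the window and she counts as a non-starter |

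Under either workable reading a historical start disappears. A prospective woman found by record screening before a post-launch appointment, who starts after it, is observed starting.

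**3. Size per woman.** Expected control events: 100 × 0.02 = 2. If 3 of 100 truly started and one is lost, the recorded rate is 2/99 = 2.0% (excluded) or 2/100 = 2.0% (not counted), against 3.0%. One woman moves the rate by about 1 point, which is half its expected value.

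**4. Window overlap.** A window opened on 14 November 2022 closes at launch, so any later index date crosses it. Two hypothetical index dates:

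- 14 May 2023: the window is 366 days, of which 14 November 2023 to 14 May 2024 is 182 days; 182/366 = 50% after launch.
- 1 October 2023: 322 of 366 days; 322/366 = 88% after launch.

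The article does not give the controls' actual dates.

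**5. Sensitivity to the historical rate (assumed range).** Power with 100 controls, 57 clients and 20% prospective uptake:

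| Historical rate | Normal approximation | Fisher's exact |
|---|---|---|
| 1% | 97.1% | 98.9% |
| 2% | 94.8% | 96.6% |
| 3% | 91.4% | 92.5% |
| 5% | 81.1% | 79.8% |
| 8% | 58.6% | 55.3% |
| 10% | 42.4% | 39.0% |

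For the estimate itself: if the true historical rate were 5% and lost starters made it look like 2%, the apparent difference would be 20 − 2 = 18 points instead of 20 − 5 = 15. The article has no data on visits per woman, so this is a range and not a prediction.

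**The case against.** A reader might infer that the two cohorts are given different time zeros and so share no valid one. The article does not say that. It states one 12-month outcome for both periods, promises comparable prospective data, and uses the same wording for both in the analysis section. What can be shown is that the visit is not fixed.

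Other counter-arguments also have force:

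- The exclusion of ever-users applies to the whole study population. A prospective woman who started years earlier is excluded too, so most depletion of earlier starters is common to both cohorts. The asymmetry is confined to controls who started between two visits inside the control sampling period.
- The article does not say how often women return to these clinics. For a control with a single visit in the period, *last* does no harm.
- Clients for the primary analysis are recruited as they attend the Service, so an enrolled client would not be dropped because she later returned to clinic.
- The stated purpose of the chart review is to establish use before implementation, and exact calendar limits may stand in the full protocol. Overlap would in any case be conservative for the Service.
- The visit date is extracted, so overlap can be examined once start dates are known. It is not inseparable from the Service effect.

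These points narrow the concern without removing it. The *last* visit rule and the undated exclusion are stated in the article, and a stated purpose does not limit follow-up. Opposite biases need not cancel.

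**Conclusion.** The point holds in a limited form. Applied as written, the control rule can lose historical starters among repeat attenders and can count starts made after the Service opened. The first lowers the historical rate and the second raises it. The net direction and size cannot be derived from the article, because visit frequency and control index dates are not given.

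It still deserves correction because the comparator is expected to rest on about 2 events, so one or two misclassified women change it materially. Against the planned 20%, such a shift is unlikely to reverse a large effect: power stays near 80% even at a 5% historical rate. The exposure is mainly in the size of the estimated difference and in the decision whether to adjust the sample size. The conclusion assumes that some controls attended more than once in the sampling period, or that some were indexed after about 14 November 2022. If neither is so, nothing is lost.

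**What to change.** 1. Define the same index visit in both cohorts: the first eligible catchment consultation in a stated calendar period. Use that term in both the outcome and the analysis sections.
2. Judge never-user status at that visit and count starts for 12 months from it.
3. Do not report control starts after 14 November 2023 as pre-implementation uptake. Add a sensitivity analysis that either censors controls at launch or is limited to controls whose 12-month window closed before launch. If censoring is used, estimate 12-month uptake with a method that allows for unequal follow-up.
4. State that each woman may enter one cohort only.

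Cost: re-dating the index visit in the 100 charts already abstracted, possibly some re-contact to confirm start dates, and slightly fewer fully observed controls in the sensitivity analysis. Keeping the launch restriction in a sensitivity analysis avoids moving the whole control group further back in time, which would add to any secular trend between the cohorts.
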